**Fig. 2 Fig2:**
[figure not shown]
Research model of the experimental conditions and outcomes

In addition to the primary hypotheses, several exploratory analyses will be conducted to investigate inter-individual differences at baseline measurements and their impact on physiological, affective, self-evaluative, and relationship variables in the laboratory setting. For instance, it will be examined whether participants who self-report higher levels of empathy and are tested to confirm this at baseline are expected to demonstrate a greater willingness to swap places with their partner and take over the alleged stress tasks their partner is enduring, as opposed to opting to remain in the supporter role. Furthermore, participants may have differing perceptions of autonomy when providing support, which could potentially impact their physiological, affective, self-evaluative, and relationship responses,  even without deliberate manipulation of autonomy. Differences in relationship satisfaction might moderate processes of support provision and perception. The engagement and emotional tone of the chat messages created in conditions with support provision might relate to providers’ outcomes as well. Additionally, baseline survey data will be utilized to validate the  latest version of the Multifaceted Empathy Test (MET-core-2 ; [63, 64]).

## Methods

### Ethics approval, funding and registration

This study forms part of a larger research project funded by the German Research Foundation (DFG #465093987). This protocol concerns the laboratory part of the study (Study 2). Ethical approval was obtained from the Ethics Committee of the MSB Medical School Berlin (#MSB 2023 − 138) and the study complies with the 1964 Declaration of Helsinki. All participants provide informed consent prior to data collection. Three further studies are part of the PROSPECT research program, one on video observed support provision in dyads (Study 1), the other two on naturalistic support provision in ecological momentary assessments (Study 3 and 4) funded by the National Science Centre Poland (NCN #2020/39-G/HS6/02216). The study was pre-registered at the Open Science Framework (https://osf.io/csqa8/). It was also retrospectively registered with more details at the WHO registry ‘German Register for Clinical Studies’ (DRKS: https://www.drks.de/DRKS00034287).

### Study design

The laboratory study consists of two parts. In Part I, participants complete the baseline measures in an online survey in a self-chosen environment. In Part II, participants take part in the newly developed experimental paradigm at the MSB Medical School Berlin, Germany. See Fig. 3 for an overview of timepoints and Table 3 for a summary of measures.

**Fig. 3 Fig3:**
[figure not shown]
Phases of the study procedure

Part I – Online Survey (baseline). In the first part of this study, participants individually complete the baseline assessment as an online questionnaire on the survey tool SoSci Survey. This questionnaire assesses inclusion and exclusion criteria for the laboratory part, demographics, as well as a series of self-report questionnaires and an empathy test (see measures section).

Part II – Experimental paradigm with manipulation of conditions. The second part of this study will directly manipulate competence and relatedness as potential conditions for effects on immediate physiological, affective, self-evaluative, and relationship outcomes in an experimental paradigm. Participants are invited into the laboratory together with a close dyadic partner. Both dyadic partners are led to believe that their partner person is enduring several runs of stressful tasks in another room of the laboratory. In three conditions, participants will be able to provide social support to their partner persons via text messages in a computer chat window. In two of these conditions, they receive feedback, either that their messages reduced the stress of their partner person (competence condition) or that their partner person feels related to them because of their messages (relatedness condition).

### Conditions

The participants will individually and randomly assign to one of four conditions:

No support provision (observation condition = control, see Table 1)Autonomous support provision without feedback (autonomous support provision only condition, see Fig. 4)Autonomous support provision with feedback on competence (autonomous support provision + competence condition, see Fig. 5 and Table 2)Autonomous support provision with feedback on relatedness (autonomous support provision + relatedness condition, see Fig. 4 and Table 2)

Detailed instructions for each condition are available in the study material folder of the German part of the project on OSF (https://osf.io/csqa8).

**Table 1 Tab1:** Questions for participants in the observation condition (translated to English)

Question nr.	Question
1	How do you think is your partner person feeling at the moment?
2	What do you think is your partner person thinking right now?
3	How do you feel when observing your partner person's stress and pain levels?
4	What do you think when observing your partner person's stress and pain levels?
5	What do you think your partner person will tell you about the stress test afterwards?

**Fig. 4 Fig4:**
[figure not shown]
Screenshot of the alleged stress and pain levels their partner persons felt in the support provision conditions (translated to English)

**Fig. 5 Fig5:**
[figure not shown]
Screenshot of competence condition, in which the stress dropped after participants provided supportive chat messages to their allegedly stressed partner persons (translated to English)

**Table 2 Tab2:**
[figure not shown]
Feedback providers received in the competence and relatedness conditions after they provided supportive chat messages to their allegedly stressed partner persons (translated to English)

Feedback is sent by the research investigators via chat messages

### Randomization

Individual randomization is based on a computer-generated allocation plan. Once a dyad has been scheduled to participate in the second part of the study, each individual is assigned at random to one of the four conditions. For this purpose, the random sequence of conditions is created as a pre-defined list via the online generator (https://www.randomizer.org/).

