**Methods:**

A priori power analyses resulted in a planned sample size of 250 participants randomized to four conditions: 1) no support provision, 2) support provision without feedback, 3) support provision with feedback on competence, 4) support provision with feedback on relatedness. Primary outcomes are immediate physiological (saliva cortisol, heart rate, heart rate variability, blood pressure), affective (positive and negative affect, anxiety), self-evaluative (e.g., self-esteem) and relationship outcomes. Generalized linear models will be used to compare the four conditions.

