### Blinding

Participants are blinded about the true purpose of the experiment. All participants are told that the study investigates the effects of *receiving* social support on stress. In the laboratory part, participants are told that a random lottery ticket decides which dyad partner undergoes several runs of a stressful task, while the other dyad partner is observing their stress and pain levels and, depending on the condition, has the opportunity to provide support via chat messages. Each participant is always assigned  the support provider role on their lot. Each participant is made to believe that their partner person is undergoing a stressful task, when in fact neither of them is doing the stressful task. None of the participants know that the study is investigating the effects of providing support on stress and that different conditions are being tested. At the end of the experiment, participants receive a detailed debriefing based on Mills’ procedure for explaining experiments involving deception [65]. The original German version and an English translation of the debriefing conducted by our research assistants can be found at OSF (https://osf.io/8spzw).

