### Sample size calculation

Meta-analyses summarizing effects of experimental manipulations of prosocial behaviour on well-being resulted in small- to medium-pooled effects sizes from Cohen’s d = .28 [33] to Pearson’s r = .32 (corresponding to a Cohen’s d = .68; 43). Whereas these effect sizes represent support provision vs. no support provision, we are particularly interested in manipulating and comparing the effects of different conditions under which support is provided. Therefore, we base our power analyses on a small n^2^ of 0.02 for the interaction term of time*condition (Cohen, 1992; effect size f = 0.17). We deem a power of 95% desirable to detect effects not only between the ‘support’ to ‘no support’ group, but also between the groups that provide support under different conditions. With 4 between- and 2 within-subject factors entered into a repeated measures ANOVA, G*power estimates a total *N* = 216 (54 per group) to result in a 95% chance to reject the null hypothesis of no significant interaction term [66]. To allow for attrition due to failed manipulation (e.g., participants provide no support despite randomized to chosen support groups), we plan to recruit 250 participants randomized to four groups (125 dyads).

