### Planned analyses

Analyses of variance and linear mixed models between conditions and pre- and post-assessments will be performed on self-reported self-evaluative and affective as well as, physiological data and relationship variables. Of particular interest will be changes in positive and negative affect and ratings of competence and relatedness depending on the condition.

Data from participants who do not complete the full manipulation (that drop-out before the post-assessment) or show suspicion (e.g., enter trick questions into the chat boxes in order to check, whether they chat with their partners) will be analysed separately in per protocol and intention-to-treat analyses. No outliers are expected in the self-report data. In the event that participants fail to comply with the inclusion criteria for cortisol assessment (no strenuous exercise, food, alcohol, tooth brushing, smoking, caffeine, or cortisol affecting medication prior to the experiment), their cortisol data may have to be excluded post-hoc. Women who take oral contraceptives are included in the sample. For physiological data (cortisol, heart rate, heart rate variability, blood pressure) we consider truncation at 2 SD from the sample mean if outliers occur. Missing data will be handled via Full Information Maximum Likelihood (FIML).

In exploratory qualitative content analyses, we will investigate type and amount of support messages written into the computer chat boxes by participants in the three support provision conditions.

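### Partners from 125 dyads are individually randomised and both analysed, but no stated model lets them correlate: standard errors are too small for H1 (and less so H2, H6), and precision is lost for H3–H5

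*Protocol article*

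**What the plan says.** - **Allocation** (Randomization): after a dyad is scheduled, "each individual is assigned at random to one of the four conditions".
- **Both partners are providers** (Blinding): "Each participant is made to believe that their partner person is undergoing a stressful task, when in fact neither of them is doing the stressful" […]. Each partner therefore contributes a full set of outcomes.
- **Sample size** (Sample size calculation): the effect is a "small n^2^ of 0.02 for the interaction term of time*condition" in a repeated measures ANOVA, for which "G*power estimates a total *N* = 216 (54 per group) to result in a 95% chance" of rejecting the null. Allowing for attrition, "we plan to recruit 250 participants randomized to four groups (125 dyads").
- **Analysis** (Planned analyses): "Analyses of variance and linear mixed models between conditions and pre- and post-assessments will be performed". The Abstract (Methods) says: "Generalized linear models will be used to compare the four conditions".

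The article names no dyad effect, clustered standard errors, within-dyad correlation or partner non-independence.

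**The concern.** Partners come to the laboratory together and rate the same relationship (satisfaction, that day's interaction quality, closeness). Their responses may well be correlated. ANOVA and generalized linear models, as named, assume independent persons, and so does the power calculation. Two things are at stake.

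- **Validity**, for effects that are not randomised within pairs. H1 tests the response across all participants, H2 the association with trait empathy, and H6 includes a path from self-reported competence and relatedness to outcome.
- **Efficiency**, for the randomised comparisons H3–H5. With four equally likely conditions allocated independently, a pair is discordant with probability 1 − 4 × (1/4)² = 75%. Those pairs carry within-dyad information that an independent-persons analysis discards.

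**Working it through.** **Inputs.** From the protocol: four groups, 125 dyads, N = 216, η² = 0.02, power 95%. Not given, and assumed: α = 0.05, two time points, pre-post correlation ρ = 0.5, and a within-dyad correlation of the pre-post *changes* (ICC below) of 0.2, 0.3 or 0.5.

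**1. The plan's own figure.** For the within-between interaction, λ = f²·N·m/(1 − ρ), with df1 = 3 and df2 = N − 4. With η² = 0.02, f² = 0.02/0.98 = 0.0204 (f = 0.143), so λ = 0.0204 × 216 × 2/0.5 = 17.6 and power is 95.2%. The smallest N for 95% power is 216, so the plan's figure is reproduced with independent persons and no dyad term. (The printed "effect size f = 0.17" does not match η² = 0.02 and would give N = 156 at ρ = 0.5. That is a separate point.)

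**2. Randomised contrasts, dyad ignored.** The design effect is 1 + ICC(outcome) × ICC(condition). Under individual allocation ICC(condition) is about 0, so the design effect is about 1. Simulating change scores (108 dyads, 10,000 runs per scenario) confirms this:

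- type I error of the interaction test is 4.7–5.0% at ICC 0.3 and 0.5;
- the average naive standard error of a pairwise contrast at ICC 0.5 is 0.1935, against a true 0.1936;
- power stays at 95.1% (ICC 0.3) and 94.8% (ICC 0.5).

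**3. Randomised contrasts, dyad modelled.** Contrast variance is multiplied by 1 − ICC².

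| ICC of change | Variance factor | Interaction power at N = 216 | N for 95% power |
|---|---|---|---|
| 0 | 1.00 | 95.2% | 216 |
| 0.2 | 0.96 | 95.9% | 208 |
| 0.3 | 0.91 | 96.8% | 196 |
| 0.5 | 0.75 | 98.9% | 164 |

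**4. H1, overall pre-post change, dyad ignored.** Both partners contribute to the same mean, so the true variance is (1 + ICC) times the naive one. The true error rate is 2 × [1 − Φ(1.96/√(1 + ICC))].

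| ICC of change | Naive SE / true SE | True type I error |
|---|---|---|
| 0.2 | 0.91 | 7.4% |
| 0.3 | 0.88 | 8.6% |
| 0.5 | 0.82 | 11.0% |

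The simulation gives 8.4–8.5% at ICC 0.3 and 10.0–11.1% at ICC 0.5.

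**5. H2 and H6.** The inflation is 1 + ICC(outcome) × ICC(predictor). With an assumed within-dyad empathy correlation of 0.3, the factors are 1.06, 1.09 and 1.15, and the H2 error rate is about 6–7%. The mediator-to-outcome path in H6 behaves the same way if partners' mediator scores correlate.

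**6. Which dyad term works.** A dyad random intercept adds the same amount before and after, so it cancels from the change. With 125 dyads, change variance 1 and change ICC 0.5, the model standard error for H1 stays at √(1/250) = 0.0632, while the true value is √(1.5/250) = 0.0775. A dyad-by-time effect, or a covariance between partners' changes, is needed to close that gap.

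**The case against.** Four points can be made against this.

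- **The comparisons that matter most are sound.** The primary objective and the powered interaction are randomised contrasts, and their naive tests keep their error rate. This stands in full. A reader might infer that pairing makes standard errors wrong throughout, or that N must rise by a factor of 1 + ICC. The documents do not support either. That would require whole dyads to share a condition, where the simulated interaction error would be 11.3% at ICC 0.3 and 16.0% at ICC 0.5. This protocol allocates individuals.
- **Shared levels are not shared changes.** Stable similarity between partners cancels from a pre-post difference, and each partner reacts to an on-screen display, mostly under a different condition from the other. This also stands. The H1 inflation depends on correlated changes, for which there is no figure, and it vanishes if that correlation is zero.
- **H1 is labelled a manipulation check, and the H2 inflation is modest.** This is true and limits the consequence. H1 is nevertheless listed among the main hypotheses, across four outcome domains.
- **An article leaves random effects to the analysis plan, and a mixed model can carry a dyad term.** This is fair for the mixed models, and an unseen plan may already include one. It does not cover the ANOVA and generalized linear models, or a sample-size paragraph that counts 125 dyads but powers on independent persons.

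**Conclusion.** The point holds in limited form. The stated analyses and sample size do not reflect the pairing that the design creates. For H3–H5 and the powered interaction the cost is efficiency only: 4%, 9% or 25% of contrast variance at an assumed change ICC of 0.2, 0.3 or 0.5, with nominal error and an adequate N. For H1 the test is anti-conservative, at about 7.4%, 8.6% or 11% instead of 5%. H2 is affected less, and H6 in the same direction, each only if partners' predictor scores correlate.

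The direction follows from the design whenever partners' changes are positively correlated. The sizes rest on the assumed ICCs, and the power figures also on a pre-post correlation of 0.5. The documents supply neither.

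**What to change.** - Analyse H1–H6 with mixed models that let partners correlate in the change, through a dyad-by-time random effect or a dyad-level covariance, in place of plain ANOVA or generalized linear models. A dyad random intercept is enough only where the outcome is post-only or is the post value adjusted for baseline.
- Alternatively, for H1 and H2, use standard errors clustered by dyad.
- In the H6 mediation bootstrap, resample dyads, not persons.
- State in the sample-size paragraph that the 250 participants are 125 pairs, that allocation is individual, and that no inflation of N is needed for the condition contrasts.

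The cost is one or two extra variance terms, and a dyad identifier must be kept in the anonymised data. Recruitment and conduct do not change. The Data Availability section says that data collection was still under way, so the change could be specified before analysis.

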### Blinding

Participants are blinded about the true purpose of the experiment. All participants are told that the study investigates the effects of *receiving* social support on stress. In the laboratory part, participants are told that a random lottery ticket decides which dyad partner undergoes several runs of a stressful task, while the other dyad partner is observing their stress and pain levels and, depending on the condition, has the opportunity to provide support via chat messages. Each participant is always assigned  the support provider role on their lot. Each participant is made to believe that their partner person is undergoing a stressful task, when in fact neither of them is doing the stressful task. None of the participants know that the study is investigating the effects of providing support on stress and that different conditions are being tested. At the end of the experiment, participants receive a detailed debriefing based on Mills’ procedure for explaining experiments involving deception [65]. The original German version and an English translation of the debriefing conducted by our research assistants can be found at OSF (https://osf.io/8spzw).

### Sample size calculation

Meta-analyses summarizing effects of experimental manipulations of prosocial behaviour on well-being resulted in small- to medium-pooled effects sizes from Cohen’s d = .28 [33] to Pearson’s r = .32 (corresponding to a Cohen’s d = .68; 43). Whereas these effect sizes represent support provision vs. no support provision, we are particularly interested in manipulating and comparing the effects of different conditions under which support is provided. Therefore, we base our power analyses on a small n^2^ of 0.02 for the interaction term of time*condition (Cohen, 1992; effect size f = 0.17). We deem a power of 95% desirable to detect effects not only between the ‘support’ to ‘no support’ group, but also between the groups that provide support under different conditions. With 4 between- and 2 within-subject factors entered into a repeated measures ANOVA, G*power estimates a total *N* = 216 (54 per group) to result in a 95% chance to reject the null hypothesis of no significant interaction term [66]. To allow for attrition due to failed manipulation (e.g., participants provide no support despite randomized to chosen support groups), we plan to recruit 250 participants randomized to four groups (125 dyads).

## Participants

### Eligibility criteria

The following main criteria must be fulfilled for participation in the study: (1) age between 18 and 65 years; (2) informed consent to all aspects of the study; (3) proficiency in German language; and (4) joining the laboratory part of the experiment with another person (romantic partner or friend) with whom they have shared a close relationship for at least six months.

Participants who fulfill the following exclusion criteria will be excluded from participation in the study: (1) psychology students in their 5th or higher bachelor's semester or in the master's program or persons who have completed their psychology studies or (2) with a body mass index (BMI) over 30 [67]; pregnancy or breast feeding [68–70]; heavy smoking (defined as more than 10 cigarettes/day; [69, 71]); substance abuse [67, 69–71]; the presence of cardiovascular disease [67–71] or a neurological, psychiatric or endocrine disorder [67, 68, 70, 71] or the regular intake of hydrocortisol medication [69–71] as these could influence the physiological stress response [72].

### Recruitment

Study participants are recruited by distributing flyers at the Medical School Berlin (MSB), the Free University Berlin (FU) and other universities in Berlin, as well as in the area around the campus of the Medical School Berlin (e.g., neighborhood, cafés, restaurants, stores) and at public events related to psychology or research (e.g., Open Campus Day, Long Night of Science). Study participants are also recruited online through entries on online platforms (e.g., social media).

Individuals who meet the inclusion criteria are asked to give a written informed consent. The research team ensures confidentiality of this data by keeping questionnaire and physiological data and the consent forms in different data storages, to which only research assistants have access. Sensitive data (i.e., phone numbers and email addresses) will be stored only during the data collection period. Once data collection is completed, data will be anonymized and analysed statistically in this form.

### Allowance

Participants enter a lottery for 5 x 50 Euro online shopping vouchers upon completing the online baseline questionnaire and students can choose between entering the lottery or receiving research participation credit. Participants receive 30 Euro per person for taking part in the laboratory part of the trial and students can choose between the 30 Euro or 3-4 hours of research participation credits per person.

